#### Cognitive control training (CCT)

The cognitive control training (CCT) is an adaptive Paced Auditory Serial Addition Task (PASAT), adapted from that implemented in several studies investigating cognitive control training in the context of depression/rumination (e.g., [45, 46, 50]).

Participants are presented via headphones with a continuous stream of digits (1–9), with the task of immediately calculating the sum of the last two digits heard and clicking a corresponding button (1–18). Each session starts with an inter-stimulus interval (ISI) of 3000 ms, which is reduced by 100 ms following four consecutive correct responses or increased by 100 ms following four consecutive incorrect responses. Thus, the difficulty of the task is adapted to the participant’s performance and increases as their performance improves. Participants receive feedback on their performance via presentation of their ISI and number of consecutive correct/incorrect responses throughout the task. Each session consists of 400 trials (to result in a session length approximately equal to that for the PMIT). Participants can ‘pause’ the task at any time to take a break if desired. Training success is indicated by the decrease in ISI over the course of training. The CCT program is implemented as a desktop application written in Java.

Preliminary research has indicated potential for the adaptive PASAT in reducing symptoms of depression amongst people with current or remitted major depression in conjunction with an attention training paradigm [46, 50, 51], and on its own [45, 52, 53].

#### Treatment as usual (TAU)

Treatment as usual (TAU) may include individual and group psychotherapy sessions and other therapeutic activities in the clinic, and possible pharmacotherapy. The treatment offered in the participating clinics follows primarily CBT principals and includes a multimodal range of intensive individual and group therapies. This can be complemented by sports, movement, relaxing, music, ergo, creative, and art therapy, according to the individual patients’ needs. Participants in all conditions receive TAU.

Participants in the TAU condition also complete “monitoring,” a set of computerized self-report questions about mood/cognitions over the previous day (see the Measures section below) on the computer 8 times over the 2-week intervention period (< 5 mins per completion). These questions are also included at the start of every training session in the other two conditions. There are two main reasons for including these monitoring questions in the TAU group. First, monitoring can in itself have beneficial effects, e.g., via repeated reflection on one’s own progress during treatment, and completing the computerized questionnaires involves a meeting with the research staff. Including the “monitoring” in the TAU group therefore allows it to also control for these non-specific aspects of the intervention groups. Second, completion of the monitoring in the TAU group provides data on the trajectory of these measurements over time in the absence of the cognitive training interventions, providing a comparison for the other conditions. The program for the monitoring ratings is implemented as a desktop application written in Java.

### Measures

See Table 1 for a tabular display of the measures and their schedule of administration. Additionally, information on patient enrolment, adherence, and attrition rates will be collected to inform decisions around feasibility and presented as part of publication of the trial results, although no formal specific feasibility outcome was pre-specified.

**Table 1 Tab1:** Study measurement schedule

	Eligibility	Pre-training/baseline	During training	Post-training	Follow-up
Consent	x				
Demographics, clinical information	x				
DIPS-/Mini-DIPS-OA	x				
DARS	x			x	x
PANAS-P		x		x	x
QIDS-SR		x		x	x
GAD-7		x		x	x
PMH		x		x	x
PIT		x		x	
SST		x		x	
STIAT		x		x	
CEQ		x			
Feedback					x
Mood monitoring			x		

*DIPS-/Mini-DIPS-OA* Diagnostisches Interview für psychische Störungen-Open Access, *DARS* Dimensional Anhedonia Rating Scale, *PANAS-P* Positive and Negative Affect Schedule–21-item positive subscale, *QIDS-SR* Quick Inventory of Depressive Symptomatology–Self-Report, *GAD-7* Generalized Anxiety Disorder Scale, *PMH* Positive Mental Health Scale, *PIT* Prospective Imagery Test, *SST* Scrambled Sentences Test, *STIAT* Single-Target Implicit Association Test, *CEQ* Credibility/Expectancy Questionnaire

### Primary outcome

#### Positive subscale (21 items) from the extended Positive and Negative Affect Schedule (PANAS-S [54])

This measure of positive affect comprises the joviality, self-assurance, attentiveness, and serenity subscales of the extended PANAS [54], and its use in this study follows previous experimental research examining the effect of positive mental imagery on state mood (e.g., [25–27]). In the current study, the PANAS-P is administered with the ‘past week’ instructions (i.e., participants are asked to rate how much each item applies to how they have been feeling ‘in the past week, that is, during the past 7 days, including today’), and the German translation of the scale [55] is used. The individual positive subscales have shown good internal consistency (Cronbach’s alpha) in a German community sample (joviality: α = 0.92; self-assurance: α = 0.78; attentiveness: α = 0.79; serenity: α = 0.81 [55]). The primary outcome relates to the PANAS-P at post-training (i.e., about 2 weeks post-baseline). The PANAS-P is also completed at pre-training and follow-up.

### Secondary outcomes

#### Dimensional Anhedonia Rating Scale (DARS [38])

The DARS is a self-report measure of different facets of anhedonia (desire, motivation, effort, and consummatory pleasure) across different hedonic domains (hobbies/past-times, food/drinks, social activities, and sensory experiences). In the current study, an extended 26-item version (which includes extra items to measure motivation) provided by the scale authors is used, in a German translation by [name] (Ruhr-Universität Bochum, Germany), in conjunction with SEB and the scale authors. The original 17-item English-language version of the DARS has shown good convergent and divergent validity, and high internal consistency (Cronbach’s alpha) across both community (α = 0.92) and patient (α = 0.96) samples. The baseline administration of the DARS is at the eligibility assessment rather than the pre-treatment assessment for practical reasons (in order to reduce the time spent completing questionnaires prior to completing the introductory training session), and the DARS is repeated at post-training and follow-up.

#### Quick Inventory of Depressive Symptomatology (QIDS-SR [56])

The QIDS-SR was designed as brief self-report measure of depressive symptoms that specifically assesses core criterion DSM-IV symptoms of depression. It has been validated against established clinician rating scales for use in clinical trials [56]. The German translation provided by the scale publishers (http://www.ids-qids.org/) is used, which has shown acceptable internal consistency (Cronbach’s alpha = 0.77) in a sample of depressed German adults waiting for psychotherapy [57]. The QIDS-SR is completed at pre-training, post-training, and follow-up.

#### Generalized Anxiety Disorder Scale (GAD-7 [58])

This measure is a brief (seven items) self-report anxiety questionnaire designed as a screener for Generalized Anxiety Disorder in primary care. The German translation [59], which has shown high internal consistency (Cronbach’s alpha = 0.89) and construct validity in a large general community sample [59], is used. The GAD-7 is completed at pre-training, post-training, and follow-up.

#### Positive Mental Health Scale (PMH [9])

This questionnaire consists of 9 items designed to assess positive mental health. The measure (original in German) has been used in previous longitudinal research and shown to predict remission from specific phobia and suicidal ideation [10, 13]. Psychometric evaluation of the German PMH has shown good psychometric properties in student, patient, and general community samples, including good internal consistency (Cronbach’s alpha across all groups, α = 0.93), convergent and divergent validity, and sensitivity to therapeutic change [9]. The PMH is completed at pre-training, post-training, and follow-up.

#### Prospective Imagery Test (PIT [60, 61])

The PIT is a measure of the vividness with which people can imagine positive or negative events happening in their future. Participants read a list of hypothetical positive and negative future scenarios and are asked to form a mental image of each, before rating how vivid their image is from 1 (not at all vivid) to 5 (very vivid). Each assessment includes five positive and five negative hypothetical future situations, with a different set at baseline and post-treatment. A German translation [62] is used. Internal consistency (Cronbach’s alpha) has previously been good in a mixed (patient and healthy control) German sample for both the positive (α = 0.89) and negative (α = 0.83) subscales [62]. As a mechanism measure, the PIT is completed at pre-training and post-training only.

#### Scrambled Sentences Test (SST [63, 64])

This is a measure of interpretation bias, in which the participants are presented with a set of 20 scrambled sentences (e.g., “winner born I am loser a”) and instructed to write a number above five of the six words in order to construct a grammatically correct sentence, while holding in mind a six digit number (‘cognitive load’). This measures the tendency of participants to interpret ambiguous information either positively (“I am a born winner”) or negatively (“I am a born loser”). Participants will complete different versions at baseline and post-intervention. A German version translated by MLW and KW, with reference to a previous German version [65], will be used. As a mechanism measure, the SST is completed at pre-training and post-training only.

#### Single-Target Implicit Association Test (STIAT [66])

A Single-Target Implicit Association Test will be used to assess automatic associations between positive/negative affect relevant attributes and targets related to the self. Scoring is according to the algorithm by Greenwald, Nosek, and Banaji [67]. As a mechanism measure, the STIAT is completed at pre-training and post-training only.

### Other measures

#### Demographics and clinical information

Participants will complete demographic information, plus information about German language proficiency, whether they are taking any medication (and provide details if so), the duration of their stay in the clinic so far, and the reason they are in the clinic (in a few words).

#### Diagnostisches Interview für psychische Störungen–Open Access (DIPS-OA [68])/Diagnostisches Kurzinterview bei psychischen Störungen–Open Access (Mini-DIPS-OA [69])

The DIPS-OA or the shorted version Mini-DIPS-OA is a structured clinical interview, previous published versions of which have been demonstrated to be valid diagnostic tools for use with both outpatients and inpatients in psychiatric settings (e.g., [70]). The most recent version (for DSM-5) will be used, with a shorted version (Mini-DIPS) used if necessary to shorten assessment times. The structured clinical interview will be audio-recorded, provided that participants provide specific consent for this.

#### Credibility/Expectancy Questionnaire (CEQ [71])

The CEQ is a widely used measure of treatment credibility and expectancy of symptom improvement. A German version adapted from that by Riecke, Holzapfel, Rief, and Glombiewski [72] will be used.

#### Self-report mood/cognitions over the previous day

In order to provide repeated measures of potential mechanisms of change, at the beginning of each training session, participants will make a series of ratings about their mood and cognition over the previous day. Participants will rate the mood words: happy, sad, calm, anxious, optimistic, hopeless, and the following statements “Positive thoughts seem to pop into my head,” “Negative thoughts seem to pop into my head,” “I have been able to look forward to activities and events,” “I have been able to enjoy taking part in activities or events,” “I was an active person and accomplished the goals I set out to do.” (this last item taken from the Behavioral Activation for Depression Scale [73], German version by [74]). Ratings are made on the scale used for the PANAS (i.e., from 1 = not at all to 5 = extremely). These ratings are integrated into the beginning of the training sessions for the PMIT and CCT conditions, and in stand-alone Java program for the TAU condition.

#### State mood change

At the beginning and end of every training session (integrated into the computer program), participants in the PMIT and CCT groups will rate the following words according to how they are feeling “right now/ in the past few minutes”: happy, sad, calm, anxious, optimistic, and hopeless. Ratings are made on the scale used for the PANAS (i.e., from 1 = not at all to 5 = extremely).

#### Feedback questionnaire

At follow-up, participants will complete a feedback questionnaire developed for the study, which includes questions about acceptability and perceived usefulness of the intervention and questions to assess potential demand.

### Procedures

Table 1 illustrates the schedule of measurement and testing. All study assessments are carried out by a member of the research team.

#### Eligibility assessment

Following written informed consent, participants will complete background/demographic information and a structured clinical interview (DIPS-/Mini-DIPS-5), and eligibility criteria will be confirmed. The pre-training/baseline administration of the Dimensional Anhedonia Rating Scale (DARS) will be completed at this assessment (for practical reasons, to shorten the pre-training/baseline assessment).

#### Pre-training/baseline assessment

Participants will complete baseline measures (PANAS-P, PMH, QIDS-SR, GAD-7, PIT, SST, STIAT) and be randomized to one of the three conditions (TAU, PMIT, CCT). Following a brief introduction to their allocated condition, participants will complete the Credibility/Expectancy Questionnaire (CEQ). They will then complete an initial version of their allocated task, which comprises instructions (on the computer) and a brief version of the training.

#### Randomization

Randomization will be stratified by gender and by clinic, using variable block lengths and implementation via sealed envelopes so that allocation will remain unpredictable to trial staff. The randomization sequence was generated via the trial statistician (TN) using the statistical software package R version 3.3.1. Only the statistician will have access to this sequence. The statistician will sign and place the allocations into sequentially numbered opaque envelopes, with the allocation printed in pale ink so that it is not readable through the envelope. The envelope will be signed across the seal and tape placed over the signature.

Randomization will occur in the pre-training/baseline assessment after a participant has completed all baseline measures. The administering researcher will first photograph the envelope seal, then open the envelope, and write the date, time, and participant number on the allocation sheet, then sign and photograph it. These time-stamped photographs thus provide evidence of appropriate allocation and can be cross-checked against the time-stamp for the questionnaire and training data. At the end of the study, the allocations will be checked against the original allocation sequence held by the statistician (TN).

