### Setting and location

The study will take place in clinics offering inpatient treatments for mental health in Germany. The initial study site was the Nexus Klinik in Baden-Baden, Germany, with a first episode of recruitment from November 2016 to January 2017. The St. Marien Hospital Eickel, Germany, was added as an additional site in March 2017, with recruitment starting in April 2017.

The Nexus-Klinik Baden-Baden is a private clinic for psychosomatic medicine, psychotherapy and psychiatry. There are 49 therapy places available for patients suffering mainly from burn-out and stress disorders, depression, anxiety disorders, psychosomatic illnesses, chronic pain, somatoform disorders, stress and adaptation disorders as well as grief reactions, posttraumatic stress disorder, sleeping disorders, obsessive compulsive disorder, comorbid harmful use of psychotropic substances, disorders relating to sexuality, and eating disorders. The average treatment duration in 2016 was 43 days.

The St. Marien Hospital Eickel in Herne is a clinic for psychiatry, psychotherapy, and psychosomatic medicine. There are 159 therapy places available in the inpatient setting for patients suffering mainly from depression, paranoid schizophrenia and alcohol addiction, as well as anxiety disorders, bipolar disorders, traumatic- and stress-related disorders, somatic symptom disorders, schizoaffective disorders, substance-related and addictive disorders, neurocognitive disorders, and personality disorders. Patients are generally referred by their general practitioner or psychiatrist, or otherwise self-present. The average treatment duration in 2016 was 23 days.

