### Statistical analyses

In line with recommendations for pilot/feasibility studies (e.g., [47]), the purpose of this study is not hypothesis-testing, and thus it is not planned to test the statistical significance of potential differences between treatment arms on the clinical outcome measures.

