#### Outcome measures

Outcome data will be presented in the form of both raw means and standardized effect sizes at each time point, with 95% confidence intervals, for both intention-to-treat and per-protocol samples. For scales with subscales (e.g., PANAS-P, DARS), both the total scale score and individual subscale scores will be calculated. Outcome data will be presented both pooled across sites and separately per site.

The intention to treat sample will include all participants randomized to condition, and estimated means, effect sizes (between and within-group, expressed as Cohen’s *d*), and 95% confidence intervals will be estimated via fitting of a linear mixed model over the three assessment time-points (i.e., a mixed model repeated measures ANOVA). Mixed models are used for the intention to treat estimates as this allows inclusion of all participants without the need to impute missing data [75].

The per-protocol sample is defined as those participants who complete at least four of the eight training sessions (or measurement sessions in the TAU condition), including at least one in the second week of training, and who provide the required outcome data. Means, effect sizes, and 95% confidence intervals will therefore be computed from the available data.

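### Randomisation is stratified by gender and clinic, but the pooled model as described names neither, so single-time-point intervals are conservative if either factor is prognostic

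*Protocol article*

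**What the plan says.** Under Randomization, the protocol article says: "Randomization will be stratified by gender and by clinic, using variable block lengths".

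Under Outcome measures, the intention-to-treat means, effect sizes and intervals come from "fitting of a linear mixed model over the three assessment time-points (i.e., a mixed model repeated measures ANOVA". No covariate is listed. Site is dealt with in one sentence: "Outcome data will be presented both pooled across sites and separately per site". Gender does not appear anywhere in the Statistical analyses section. Effect sizes are to be Cohen's d, between and within groups, without saying which SD is the divisor. For the per-protocol sample no model is named: "Means, effect sizes, and 95% confidence intervals will therefore be computed from the available data".

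Under Setting and location, the two clinics are described as quite different. One is a private psychosomatic clinic, where "The average treatment duration in 2016 was 43 days". The other is a larger psychiatric hospital treating mainly depression, schizophrenia and alcohol addiction, where "The average treatment duration in 2016 was 23 days".

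The primary outcome is the PANAS-P at post-training, so a comparison at a single time-point is central.

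**The concern.** Stratified blocks keep the arms balanced over clinic and gender. Differences between strata therefore largely cancel out of the between-arm difference, and its true sampling variance is close to the within-stratum variance. A model without these factors leaves the between-stratum variance in its residual, so the standard error it reports is larger than the design warrants. The trial pays for the balance but does not collect the precision.

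Clinic is plausibly prognostic, given the case mix at the two sites. What is at stake is the precision of the clinical estimates. The article plans no significance tests and offers the effect sizes and their intervals as a guide to a later, powered trial, so these intervals are the main clinical result.

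**Working it through.** **Inputs from the article.** Three arms at 1:1:1 (Design); about 90 participants, 30 per arm (Sample size); three assessment time-points, the first before training (Outcome measures). Check: 3 × 30 = 90, as stated. The sample size is pragmatic, so there is no power figure to reproduce.

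**Inputs that are assumed.** The article gives no clinic or gender effect on any outcome. Both are assumed here in units of the within-stratum SD, over a range that includes zero. Also assumed: two clinics of equal size, an equal gender split, baseline-to-post correlation 0.6, a true effect of 0.5 SD and complete data.

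**Step 1, baseline precision.** The 95% half-width for a pairwise difference at one time-point is t(87) × √(2/30) = 0.513 SD, with 90 − 3 = 87 degrees of freedom.

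**Step 2, formula.** With clinic proportion p, clinic effect c and gender effect g, the added variance is v = p(1 − p)c² + 0.25g², and the share explained is R² = v/(1 + v). Leaving the factors out multiplies the width by about 1/√(1 − R²) = √(1 + v). For c = 0.5 and g = 0.3: v = 0.0625 + 0.0225 = 0.085, and √1.085 = 1.042. For c = 0.8 and g = 0.5: v = 0.16 + 0.0625 = 0.2225, and √1.2225 = 1.106. Allowing for two fewer residual degrees of freedom gives 1.041 and 1.105.

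**Step 3, simulation.** 3,000 trials, blocks of 3 or 6 within clinic-by-gender strata, contrast at post-training:

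| Clinic / gender effect (SD) | R² | Full width, factors omitted | Full width, factors included | Excess | Coverage, omitted / included |
|---|---|---|---|---|---|
| 0 / 0 | 0 | 1.020 | 1.021 | none | 95.6% / 95.5% |
| 0.3 / 0.2 | 0.031 | 1.039 | 1.023 | 1.6% | 95.1% / 94.8% |
| 0.5 / 0.3 | 0.078 | 1.067 | 1.024 | 4.2% | 95.5% / 94.4% |
| 0.8 / 0.5 | 0.182 | 1.135 | 1.025 | 10.7% | 97.0% / 94.8% |

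The estimated mean difference is about 0.50 in every row, with or without the factors. With an uneven split of 20 and 70 participants and effects 0.5 / 0.3, the widths are 1.056 and 1.023, an excess of 3.2%.

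**Step 4, change from baseline.** If stratum effects are constant over time, adding the factors changes nothing: 0.918 against 0.919 at 0.5 / 0.3, and 0.914 against 0.915 at 0.8 / 0.5. If the clinics differ in change by δ, the change score has variance 2(1 − 0.6) = 0.8 and the inflation is √(1 + δ²/(4 × 0.8)). For δ = 0.3, 0.5 and 0.8 this gives 1.014, 1.038 and 1.095. A simulation gave 1.4%, 4.0% and 9.9%.

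**Step 5, baseline as a covariate.** If the post-training contrast were adjusted for baseline score, most of the gain would already be made: 0.833 against 0.825 (1.0%) at 0.5 / 0.3, and 0.841 against 0.824 (2.1%) at 0.8 / 0.5. The article does not describe such a covariate; baseline enters as one of the modelled time-points.

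**The case against.** The strongest objection is that the article is silent rather than wrong. It is a condensed account, it never says that clinic and gender are left out, and a covariate list may stand in an analysis plan that is not shown. That limits the point: a reader might infer that the factors are definitely excluded, and the text does not establish this. It does not remove the point. The article names a specific model, defines both analysis samples and says how site is handled, and an analyst following that text would fit a model without the two factors.

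Second, the loss is conditional and errs on the safe side. This stands. With no stratum effect there is nothing to gain, and the article also says "it is not planned to test the statistical significance of potential differences between treatment arms on the clinical outcome measures", so no error rate or power is at issue. Against a half-width of about 0.51 SD, a few percent would not change a feasibility conclusion.

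Four stronger readings are tempting but are not supported:

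- **Cohen's d is understated.** At the large assumed effects, a d of 0.50 on the within-stratum SD reads 0.454 on the unadjusted SD. Dividing by the total SD is a legitimate and common choice, the raw difference is unbiased, and the article does not name its divisor. The gap is one of scale.
- **Clinic changes the time course.** Training plus follow-up takes about 14 + 14 = 28 days, between the mean stays of 23 and 43 days, so the setting of follow-up may differ by clinic. But these are clinic-wide means for 2016, and eligibility requires patients to finish training before discharge, which favours longer stays. The post-training primary outcome is not reached by this argument.
- **Per-site analyses have at most 15 per arm.** That figure is 45/3 and needs an equal split between sites, which the article does not state.
- **Per-site results must come from one joint model with a condition-by-clinic-by-time term.** This is a preference. It costs further degrees of freedom and relies on equal variances in two dissimilar clinics. The planned per-site presentation is acceptable.

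**Conclusion.** The point holds in conditional form. The design stratifies by two factors that the pooled model, as described, does not carry. If clinic or gender is prognostic, between-arm intervals at a single time-point, including post-training PANAS-P, are conservative: no wider with no stratum effect, about 4% wider at moderate and 11% at large assumed effects, with coverage up to 97.0%. These sizes rest on assumed effects, equal clinics and complete data. The treatment difference is not biased, and change-from-baseline contrasts are affected only if clinic alters the time course. It is a modest loss of precision, worth correcting because the correction costs almost nothing: 1.021 against 1.020 in width when the factors carry no information.

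**What to change.** In the Outcome measures paragraph, state that the pooled mixed model for every outcome includes clinic and gender as fixed effects, together with clinic-by-time. In the same place, state which SD divides the difference to give Cohen's d, so that a later trial can use the effect sizes on a known scale. Keep the planned per-site presentation as it is.

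The cost is one or two sentences and about four degrees of freedom out of about 90 participants: one for clinic, one for gender and two for clinic-by-time over three time-points. Measures taken only before and after training need three. If an analysis plan already lists these terms, a short reference to it in this paragraph is enough.
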